#### Risk-Benefit-Evaluation:

At each study site, two subinvestigators with clinical experience in the treatment of children with TSC will evaluate the individual risk-benefit profile of the participants treated with the IMP at 6, 12, and 18 months of life, considering the individual IMP pharmacovigilance as well as possible novel findings in the research field being considered as relevant for the respective individual. These evaluations are implemented into the study visits V6, V8, and V10. If one of the evaluating pediatricians comes to the decision that the respective participant is unlikely to benefit from continuation of IMP application, the treatment will be terminated. The participant will be continued receiving SOC and will be followed-up until the primary endpoint of the study. The results from each risk-benefit evaluation will be documented in the eCRF and on a separate, signed worksheet at the respective study visit. All decisions will be reported to the coordinating investigator.

Bayley Scales of Infant and Toddler Development III (BSID-III, cognitive scale): The BSID-III is used to assess current cognitive, language, and motor functioning levels. Within the scope of the study, only cognition is examined. During the examination, tasks arranged by difficulty are presented to the child in a predetermined order. Age-related starting points as well as reversal and exit rules allow for a differentiated and time-effective assessment of the child's developmental level. Results will be entered in the eCRF by study personnel at each site after the external examiner has completed and scored the paper-based examination.

- Raw value (Kog\_RW);
- Subtest value (Kog\_UTW);
- Scale value (Kog\_SK)

Vineland III Adaptive Behaviour Scale (VABS-3): The Vineland Adaptive Behaviour Scales - Third Edition (Vineland-3) is a multidimensional questionnaire procedure for third-party assessment of adaptive behaviour in children, adolescents, and young adults. The procedure is used, among other applications, as part of the diagnosis of intelligence impairment, developmental disorders and autism spectrum disorders. The form is completed by the participants guardian(s) or caregiver(s). The questionnaires can be administered and evaluated in paper form or in digital form via Q-global. Different scale scores (including communication, daily living skills, social skills) as well as a global score (the total adaptive behaviour score) can be determined. The Vineland Scale will be completed at 12 and 24 months of age +/- 2 weeks and results of scale scores and global scores will be entered in the eCRF by study personnel at each site after the external examiner has completed and scored the examination.

#### Communication:

- raw score listening and understanding (ZuV\_RW)
- v-scale value listening and understanding (ZuV\_v-W)
- raw value speaking (Spr\_RW)
- v-scale value speaking (Spr\_v-W)
- raw value reading and writing (LeS\_RW)
- v-scale value reading and writing (LeS\_v-W)
- communication scale value (KOM\_SW)

|                                                                    |                                              |                                |
|--------------------------------------------------------------------|----------------------------------------------|--------------------------------|
| Clinical Trial Code: PROTECT
EU trial number: 2022-502332-39-00 | Trial Protocol
(Version 06; (01.10.2024)) | Page 75 of 110
CONFIDENTIAL |
|--------------------------------------------------------------------|----------------------------------------------|--------------------------------|

Daily living skills:

- raw score Caring for oneself (Fss\_RW)
- v-scale value Caring for oneself (Fss\_v-W)
- household raw score (Haa\_RW)
- v-scale value Household (Haa\_v-W)
- raw value Living in the community (Gs\_RW)
- v-scale value living in the community (Gs\_v-W)
- everyday skills scale value (AF\_SW)

Social skills:

- raw score Interaction with others (Umg\_RW)
- v-scale value Interaction with others (Umg\_v-W)
- raw score Play and leisure (Spi\_RW)
- v-Scale value Play and Leisure (Spi\_v-W)
- raw score Adjustment (Anp\_RW)
- v-Scale Value Adjustment (Anp\_v-W)
- social skills scale value (SF\_SW)

Total value adaptive skills:

- scale value GAV (GAV\_SW)

Gross motor skills and Fine motor skills:

- gross motor skills raw score (Gmo\_RW)
- v-scale of gross motor skills (Gmo\_v-W)
- fine motor skills raw score (Fmo\_RW)
- v-scale of fine motor skills (Fmo\_v-W)
- scale value MOT\_(MOT\_SK)

Diagnostic Observation Scale for Autistic Disorders-2, toddler module (ADOS-2): ADOS-2 is a reliable, valid and clinically very descriptive procedure for the clarification and classification of qualitative abnormalities of social interaction and reciprocal communication in autism spectrum disorders. The structured rating scale belongs to the international standard of diagnostics of autistic spectrum disorders. The toddler's module is selected in order to be able to examine facts and symptoms relevant for the diagnosis of autism on the basis of specifically staged playful elements, activities and conversations in the study participant at 12 and 24 months of age +/- 2 weeks. Results of scale scores and global scores will be entered in the eCRF by study personnel at each site after the external examiner has completed and scored the examination.

Each time a test is performed, the module used for the assessment must be recorded beforehand. This is not determined by age, but primarily by language skills (e.g., fluent speech, individual words, ...).

- Item-encodings: A1-9; B1-18; C1-3; D1-5; E1-4
- Raw score Social Affect (ADOS\_SA\_RW) following conversion of item encodings into algorithm values.
- Raw score Restrictive and Repetitive Behaviors (ADOS\_RRV\_RW) following conversion of item encodings into algorithm values
- Sum SA and RRV (ADOS\_SA\_RVV\_SW)
- Age-specific comparison score (ADOS\_Vergl)
- Symptom level (ADOS\_symp)
- Diagnosis (ADOS\_Diag)

|                                                                    |                                              |                                |
|--------------------------------------------------------------------|----------------------------------------------|--------------------------------|
| Clinical Trial Code: PROTECT
EU trial number: 2022-502332-39-00 | Trial Protocol
(Version 06; (01.10.2024)) | Page 76 of 110
CONFIDENTIAL |
|--------------------------------------------------------------------|----------------------------------------------|--------------------------------|

Modified Checklist for Autism in Toddlers revised (M-CHAT-R/F) at 24 months of age: The Modified Checklist for Autism in Toddlers, Revised with Follow-Up (M-CHAT-R/F [98]) is a two-step screening instrument consisting of a parent/caregivers questionnaire to assess the risk for autism spectrum disorder (ASD). As a result, the M-CHAT returns a value depending on which a suspected autism spectrum disorder should be further clarified.

- abnormal values (Mchat), metric 0-20
- Low risk: total score 0-2; Medium risk: total score 3-7; High risk: total score 8-20; (Mchat\_risk)

Screening for TSC-associated neuropsychiatric disorders (TAND): A TAND questionnaire is completed at the participating sites by qualified study personal together with the caregivers. Following results will be entered with date into the eCRF.

Chapter 03: Behaviors (TAND\_03).

- Fears (yes/no)
- Depressed moods (yes/no)
- Severe shyness (yes/no)
- Mood swings (yes/no)
- Aggression (yes/no)
- Outbursts of anger (yes/no)
- Self-injurious behavior (e.g., hitting, biting, or scratching oneself) (yes/no)
- Failure or delayed onset of communicative speech (yes/no)
- Constant repetition of words or phrases (yes/no)
- Lack of eye contact (yes/no)
- Difficulty socializing with peers (yes/no)
- Repetitive behaviors (e.g., doing the same thing over and over) (yes/no)
- No or little flexibility in everyday situations or when deviating from routine (yes/no)
- Overactivity or hyperactivity (e.g., being constantly on the go) (yes/no)
- Difficulty with attention and/or concentration (yes/no)
- Restlessness or agitation (e.g., fidgeting, wiggling) (yes/no)
- Impulsivity (e.g., interrupting others, not being able to wait one's turn) (yes/no)
- Problems with eating behavior (e.g., eating too much or too little, unusual preferences) (yes/no)
- Sleep disturbances (e.g., unusual sleeping and/or waking times) (yes/no)

Chapter 09: Burden of problems caregiver (TAND\_09) ordinal scale 0-10

Chapter 12: Burden of problems investigator (TAND\_12) ordinal scale 0-10

|                                                                    |                                              |                                |
|--------------------------------------------------------------------|----------------------------------------------|--------------------------------|
| Clinical Trial Code: PROTECT
EU trial number: 2022-502332-39-00 | Trial Protocol
(Version 06; (01.10.2024)) | Page 77 of 110
CONFIDENTIAL |
|--------------------------------------------------------------------|----------------------------------------------|--------------------------------|

EEG: All EEG recordings will be performed by the participating sites. All recordings should be entered with date and written summary as described in the original report into the eCRF [date]. Additionally, a copy on compact disc (CD) with the patient number, study name and date must be sent to the Coordinating Investigator. A blinded centralised EEG assessment using BESA (Brain Electrical Source Analysis) Research EEG-Rater-Software will be performed at the coordinating site.

Assessments:

Overall rating [normal, conspicuous, pathological].

Slow background activity [none, mild, moderate, severe].

Epileptiform spikes [no, focal, generalized].

Number of epileptiform spike "clusters" [n], proportion of epileptiform activity [percent] per cluster.

Hypsarrhythmia [yes/no]

cMRI: Is performed according to standard of care at time of diagnosis and in 1-3-year intervals. All brain MRIs should be entered as unscheduled visits with date and written summary as described in the original report into the eCRF [date, text]. Additionally, a copy on compact disc (CD) with the patient number, study name and date must be sent to the Coordinating Investigator.

Assessments:

Overall rating [normal, conspicuous, pathological].

Cortical tubers (n), size, if applicable.

subependymal nodules (n), size, if applicable.

subependymal giant cell astrocytoma (n), size, if applicable.

Other findings [text]

Further parameters can be added at a later timepoint for future research questions which are not known at the time of consent; exploratory approach of the data for the evaluation of the examination results.

Echocardiogram: Is performed according to SOC. All examinations should be entered as unscheduled Visits with date and written summary as described in the original report into the eCRF [date, text]. Additionally, a copy on compact disc (CD) with the patient number, study name and date must be sent to the Coordinating Investigator.

Assessments:

Overall rating [normal, conspicuous, pathological].

Cardiac rhabdomyomas (n), size, if applicable.

Other anatomical abnormalities [yes, no], if yes: type [text]

heart failure [yes, no], if yes [text]

Other findings [text]

Further parameters can be added at a later timepoint for future research questions which are not known at the time of consent; exploratory approach of the data for the evaluation of the examination results.

Electrocardiogram (ECG): Is performed according to SOC. All examinations should be entered as unscheduled Visits with date and written summary as described in the original report into the eCRF [date, text].

Assessments:

Overall rating [normal, conspicuous, pathological].

Functional disturbance [yes, no], if yes [text]

arrhythmia [yes, no]

|                                                                    |                                              |                                |
|--------------------------------------------------------------------|----------------------------------------------|--------------------------------|
| Clinical Trial Code: PROTECT
EU trial number: 2022-502332-39-00 | Trial Protocol
(Version 06; (01.10.2024)) | Page 78 of 110
CONFIDENTIAL |
|--------------------------------------------------------------------|----------------------------------------------|--------------------------------|

#### Other findings [text]

Further parameters can be added at a later timepoint for future research questions which are not known at the time of consent; exploratory approach of the data for the evaluation of the examination results.

Abdominal sonography: Is performed according to SOC. All examinations should be entered as unscheduled Visits with date and written summary as described in the original report into the eCRF [date, text].

#### Assessments:

Overall rating [normal, conspicuous, pathological].

angiomyolipomas (n), size, if applicable.

kidney size [mm],

renal pelvis dilation [yes, no],

echogenicity [normal, abnormal]

Further parameters can be added at a later timepoint.

#### Laboratory analyses:

Clinical chemistry [albumin, alkaline phosphatase, ALT, AST, calcium, chloride, creatinine, direct bilirubin, total bilirubin, LDH (lactate dehydrogenase), magnesium, phosphate, potassium, sodium, uric acid, creatinine clearance (calculated)].

Haematology [leukocytes, neutrophils, eosinophils, basophiles, lymphocytes, monocytes, erythrocytes, thrombocytes, haematocrit, haemoglobin].

Lipid panel [triglycerides, total cholesterol (fasting), LDL, HDL]. The patient must be in a fasting state (2h for infants who are breastfed or receive formula milk feeding and 4h for infants and children who receive solid food) at the time of blood sampling for the lipid profile evaluation.

Urinalysis: Dipstick measurements in spot-urine for protein, ketones, bilirubin, nitrites, urobilinogen, glucose, pH and blood will be performed. Any significant findings on dipstick will be followed up with a microscopic evaluation, where WBC (White Blood Cells) and RBC (Red Blood Cells) sediments will also be measured. In the case a urine sample cannot be obtained, this test can be omitted.

After collection the samples will immediately be delivered to the laboratory for respective determinations. All parameters will be documented on appropriate eCRF-pages.

Further laboratory parameters may be determined at any time during the clinical trial at discretion of the responsible investigator. Pathological and clinically relevant findings will be documented as (S)AEs.

#### Safety laboratory analyses:

- Blood alcohol concentration (BAC)
- Surrogate parameters for potential propylene glycol (PG) intoxication: electrolytes, osmolality, creatinine, urea, pH, lactate, bicarbonate, anion gap, and the calculated osmol gap

#### Accompanying research:

- RNA samples will be collected for accompanying research at screening and 24 months (V12) (PAXgene® Blood RNA System, 2,7ml).
- DNA samples will be collected for accompanying research at 24 months (V12) of age.

|                                                                    |                                              |                                |
|--------------------------------------------------------------------|----------------------------------------------|--------------------------------|
| Clinical Trial Code: PROTECT
EU trial number: 2022-502332-39-00 | Trial Protocol
(Version 06; (01.10.2024)) | Page 79 of 110
CONFIDENTIAL |
|--------------------------------------------------------------------|----------------------------------------------|--------------------------------|

- Vaccination titres: the titers of vaccines applied during the first year (measles, mumps, rubella, tetanus, pertussis, varicella) will be assessed in both groups.

Special tubes, packaging and labels will be provided by the sponsor or his delegate(s). After sample collection, probes will be labelled and send immediately to the Institute of human genetics Leipzig for RNA and DNA, according to the investigator's manual provided by the sponsor or his delegate(s).

#### Pharmacokinetics

During the titration period, pre-dose PK blood samples will be collected immediately prior to dosing on the study day. Any sample collected outside of these parameters is not considered a true trough and therefore should not be used as a basis for adjusting the patient's dose. It is expected that all patients will achieve the desired target pre-dose trough level ( $C_{min}$ ) during the titration period (V1-V4). A local lab (at the treating centre) will measure the sirolimus concentrations. HPLC-MS/MS is the most appropriate method, other techniques (e.g. immunoassays) tend to under-/overestimating of drug concentrations. After obtaining current trough levels, the site will adjust the future dose as described in section 5.5.3 (to maintain, increase or decrease the dose). In order to minimize total blood samples, the amount of blood required for sirolimus PK samples will be 0.5 mL.

#### Therapy

The current dose and all dose adjustments (to maintain, increase or decrease the dose) of study medication [mg] will be entered into the eCRF at each study visit for the treatment group.

|                                                                    |                                              |                                |
|--------------------------------------------------------------------|----------------------------------------------|--------------------------------|
| Clinical Trial Code: PROTECT
EU trial number: 2022-502332-39-00 | Trial Protocol
(Version 06; (01.10.2024)) | Page 80 of 110
CONFIDENTIAL |
|--------------------------------------------------------------------|----------------------------------------------|--------------------------------|

## 7. Discontinuation and early Termination

Any legal guardian(s) of the subject can withdraw from the treatment or the clinical trial verbally or in writing at any time without personal disadvantages and without having to provide a reason. However, the investigator should make a reasonable effort to ascertain possible reasons, while fully respecting the subject's rights. Specifically, the legal guardian(s) of the subject must not be coerced or unduly influenced to continue to participate. Any given reason should be documented in the subject's file and in the eCRF.

The investigator can also discontinue the study medication after considering the risk-to-benefit ratio, if he / she no longer considers the treatment justifiable. The date of and the primary reason for the withdrawal (one primary reason must be determined), as well as the observations available at the time of withdrawal are to be documented in the eCRF.

For details concerning sample and statistical considerations see 9.1.

### 7.1 Temporary Discontinuation from Treatment with the IMP

Temporary treatment (IMP) discontinuation at the discretion of the investigator is defined as one or more doses not administered to the subject.

Temporary treatment discontinuation may be considered by the investigator because of the following:

- Sirolimus may affect the response to vaccination. Sirolimus should be paused 2 weeks before until 2 weeks after receiving a live vaccine. The SmPC of Sirolimus recommends avoiding live vaccines during treatment with Sirolimus. Individual risks/ benefits should be discussed with infectious disease specialists.
- Surgical interventions: Treatment with sirolimus may affect wound healing. We recommend pausing treatment 14 days before until 14 days after elective surgical interventions. For non-elective interventions, therapy should also be paused until 14 days after the procedure.
- For a single grade 3 adverse event or for less serious adverse events, e.g. uncomplicated (viral) infections, sirolimus can be temporarily discontinued at the discretion of the investigator (for details see chapter 5.5.3)
- Grade 4 adverse event (for details see chapter 5.5.3)

### 7.2 Permanent Discontinuation from Treatment with the IMP

Permanent treatment discontinuation with the IMP is any treatment discontinuation associated with the investigator's or the legal guardian(s) of the subject's definitive decision not to re-expose the subject to the IMP. The following criteria will lead to a permanent treatment discontinuation:

- Withdrawal of consent to trial participation
- Loss to follow-up
- Death
- Legal guardian(s)'s request, i.e. withdrawal of consent for treatment → documentation in source data
- Use of illicit drugs, prohibited concomitant medications (e.g. other mTOR inhibitors), or other substances that, in the opinion of the investigator, are likely to increase toxicity or otherwise confound the results while taking the IMP.
- Recurring grade 4 adverse events (AE) or serious and unexpected adverse events (SAE) related to the IMP require permanent discontinuation of sirolimus.

|                                                                    |                                              |                                |
|--------------------------------------------------------------------|----------------------------------------------|--------------------------------|
| Clinical Trial Code: PROTECT
EU trial number: 2022-502332-39-00 | Trial Protocol
(Version 06; (01.10.2024)) | Page 81 of 110
CONFIDENTIAL |
|--------------------------------------------------------------------|----------------------------------------------|--------------------------------|

- Lack of compliance, e.g. caregivers and participants fail to attend interim visits or to perform self-medication according to schedule.
- Any additional diagnosis due to which, in the investigator's opinion, participation in the treatment group of the trial may pose a risk for the study participant or that may interfere with protocol adherence.
- Negative Risk-Benefit Evaluation
- Subject did not meet in-/exclusion criteria (coming to light after inclusion), if it poses a risk for the study participant to continue the IMP in the opinion of the investigator.

The reason for the permanent discontinuation of treatment with IMP has to be documented in the source data.

Even if the trial treatment with the IMP is discontinued, the subjects may remain in the trial and, given the legal guardian(s) oral agreement (documentation in source data), will be followed-up as outlined in the schedule of assessments (further study visits according to the control group) and section 6.

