So far, no medical treatment in tuberous sclerosis is known to have an impact on neuropsychologic outcome at 24 months of age. The only study addressing effects of early treatment on neuropsychologic outcome in TSC by [14] did not show significant effects. Studies comparing vigabatrin to hormonal treatment (prednisone or ACTH) or a combination of vigabatrin and hormonal treatment failed to show differences on long-term cognitive outcome [75]. It has been shown that approved antiseizure medications in this age group, such as phenobarbital have no positive effect and can be harmful to cognitive development [76]. Overall, it can be assumed that antiseizure medications or other symptomatic treatment in TSC has no disease-modifying effect on neuropsychological outcome.

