#### **Oxcarbazepine and Carbamazepine**

Carbamazepine is approved for the treatment of focal seizures and oxcarbazepine as adjunct treatment for focal seizures in the study population. Both are sodium channel blockers. No positive effects on neuropsychological outcome are expected. As CYP3A4 inducers, pharmacologic interactions with sirolimus should be respected. Significant clinical interactions regarding primary study outcome are not expected.

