### **Rescue medications**

Midazolam (buccally, from 3 months) and rectal diazepam are approved rescue medications for prolonged epileptic seizures. They have anti-seizure effects and they can have sedative effects. Recurrent or chronic use should be avoided, as negative effects on neuropsychological outcome similar to phenobarbital can be expected.

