#### 5.6.1 Interaction with other medicinal products

The following paragraph is extracted and adopted from the "Rapamune - EPAR - Product Information, ANNEX I, SUMMARY OF PRODUCT CHARACTERISTICS, section 4.5" of the "European Medicines Agency" as of 25.07.2022 [93]:

"Sirolimus is extensively metabolized by the CYP3A4 isozyme in the intestinal wall and liver. Sirolimus is also a substrate for the multidrug efflux pump, P-glycoprotein (P-gp) located in the small intestine. Therefore, absorption and the subsequent elimination of sirolimus may be influenced by substances that affect these proteins. Inhibitors of CYP3A4 (such as ketoconazole, voriconazole, itraconazole, telithromycin, or clarithromycin) decrease the metabolism of sirolimus and increase sirolimus levels. Inducers of CYP3A4 (such as rifampin or rifabutin) increase the metabolism of sirolimus and decrease sirolimus levels. Co-administration of sirolimus with strong inhibitors of CYP3A4 or inducers of CYP3A4 is not recommended."

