#### Phenobarbital, Phenytoin (CYP3A4 inducer)

Inducers of CYP3A4 may increase the metabolism of sirolimus and decrease sirolimus blood levels. We recommend performing a trough levels of sirolimus one week after starting additional treatments with Phenobarbital or Phenytoin and adjusting the dose as directed.

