#### **5.6.2 Permitted Medication and Therapies**

Additional treatments, including rescue medication for e.g. prolonged seizures, will be administered according to standard of care and should not be influenced by the study. Special caution and possible dose adjustments are necessary with the substances mentioned in section 5.6.1).

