#### **5.6.3 Prohibited or restricted Medication and Therapies**

Patients must not take any other mTOR inhibitors while in the study.

The substances mentioned in section 5.6.1 are not prohibited or restricted, if there is medical necessity and indication. Additional pre-dose blood samples for determination of sirolimus concentrations should be collected one week after starting or changing the dose of any CYP3A4 inducer/inhibitor.

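### Section 7.2 makes an investigator's opinion that a non-prohibited drug confounds the results a ground for stopping sirolimus permanently; this non-safety ground fits poorly with section 5.6 and serves no purpose under section 9.4

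*Protocol*

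**What the plan says.** Section 7.2 introduces its list as criteria that will lead to permanent discontinuation, which it defines as a definitive decision not to re-expose the child. One bullet names illicit drugs, prohibited medications (with other mTOR inhibitors as the example) "or other substances that, in the opinion of the investigator, are likely to increase toxicity or otherwise confound the results while taking the IMP".

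Section 5.6.3 forbids only other mTOR inhibitors. For interacting drugs it says: "The substances mentioned in section 5.6.1 are not prohibited or restricted, if there is medical necessity and indication". It asks for an extra pre-dose level one week after any CYP3A4 inducer or inhibitor is started or changed. Section 5.6.2 says that additional treatments, including rescue medication, "will be administered according to standard of care and should not be influenced by the study".

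The protocol also names drugs that may affect cognition, which is the primary endpoint. Section 5.3 says that antiseizure drugs "such as phenobarbital have no positive effect and can be harmful to cognitive development". On rescue benzodiazepines it says: "Recurrent or chronic use should be avoided, as negative effects on neuropsychological outcome similar to phenobarbital can be expected". Section 5.6.1 meets phenobarbital with monitoring only: "We recommend performing a trough levels of sirolimus one week after starting additional treatments with Phenobarbital or Phenytoin and adjusting the dose as directed".

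Section 9.4 evaluates all randomized patients under the treatment policy strategy. Section 7.2 allows a child to stay in follow-up after sirolimus is stopped.

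**The concern.** The bullet gives two separate grounds for substances that are not prohibited. Because toxicity is named on its own, confounding stands as an independent, non-safety reason. The trigger is the investigator's opinion, and the stated consequence is permanent.

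The protocol itself supplies grounds for that opinion. An investigator who reads section 5.3 has reason to think that phenobarbital, or repeated rescue benzodiazepines, will affect the cognitive score. Section 5.6 would keep the child on sirolimus, with a level check for phenobarbital. Section 7.2 would end sirolimus for good.

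Controls have no study drug to stop, so the rule acts in one arm only. If sirolimus works, each such stop removes exposure without a safety reason and shrinks the contrast that the trial is meant to estimate.

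**Working it through.** **Does stopping sirolimus cure any confounding?**

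- *Primary analysis (9.4).* A stopped child is still analysed in the sirolimus arm, and the other drug is still being taken. Its effect on the score is unchanged, and only the sirolimus exposure is lost. Under treatment policy, other medication is already part of the comparison.
- *Per-protocol set (9.1).* Membership depends on at least 9 months of treatment, a 24-month BSID-III and three eligibility criteria. It has no concomitant-medication criterion. A stop before 9 months would only remove the child from this set.
- *Safety as treated (9.1).* A child randomized to sirolimus is moved to standard of care only if lost to follow-up before 6 months or never treated. A stop for confounding changes nothing here.
- *An inducer that lowers sirolimus levels.* Table 5 doubles subsequent doses when the trough is below 5 ng/ml. Stopping the drug takes exposure to zero, which is the opposite of a remedy.

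**How large could the loss be?** The protocol gives no frequency, so this is an illustration.

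Inputs from section 9.9: 30 per arm, effect 15, SD 15, 20 or 25, two-sided 5% test, 10% missing (3 per arm). Inputs assumed: one sirolimus child stopped, losing all or half of the effect.

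*The plan's own figures first.* Without missing values, power ≈ Φ(Δ/SD × √(n/2) − 1.96), with n = 30 × 3/π = 28.65 for the Mann-Whitney test under normality. For Δ/SD of 15/15, 15/20, 15/25 and 11.5/15 this gives 96.6%, 81.0%, 62.2% and 82.7%, against >95%, >80%, >62% and >80% in Table 8. Simulating the unstratified test (40,000 runs) gives 95.9%, 79.0%, 60.1% and 80.9%, within 2 points of the table's bounds. With 3 missing values per arm drawn from observed controls, simulation gives 91.1%, 70.2% and 50.9% for effect 15 at SD 15, 20 and 25. Table 8 states >90%, >70% and >50%.

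*Expected difference.* With k stopped children who each lose a share λ of the effect, and the 3 missing sirolimus values replaced from controls:

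Δ = 15 × (27 − kλ)/30

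- k = 0: 15 × 27/30 = 13.5
- k = 1, λ = 0.5: 15 × 26.5/30 = 13.25
- k = 1, λ = 1: 15 × 26/30 = 13.0

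*Power with the age-stratified test.* 40,000 simulated trials per setting, two equal age strata, control mean 75, stratified Wilcoxon (van Elteren) test:

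| SD | No stop | One stop, half loss | One stop, full loss |
|---|---|---|---|
| 15 | 90.8% | 89.6% | 88.3% |
| 20 | 69.6% | 67.7% | 65.9% |
| 25 | 50.7% | 48.9% | 47.8% |

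For one full loss the unstratified test gives 89.0%, 66.5% and 47.8%, so stratification does not drive the result.

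**The case against.** The best defence is that the residual category was meant for substances akin to illicit or prohibited ones. On that reading, the specific permission in 5.6.3 governs medically indicated drugs. The reading is possible, but 7.2 does not say it and exempts no indicated drug. It is a reason to call this poor fit rather than contradiction.

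The tension also rests on few drugs. Section 5.3 assumes that symptomatic treatment has no disease-modifying effect on neuropsychological outcome. For carbamazepine and oxcarbazepine it says: "Significant clinical interactions regarding primary study outcome are not expected". The reach is therefore narrow, and that part of the objection stands.

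A third argument is that the word results covers safety and laboratory data as well. Stopping sirolimus does not take away the other drug's effect on those either.

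Fourth, deletion leaves a gap for inducers. Section 5.6.1 advises against rifampicin and St. John's wort, and neither is described as raising sirolimus toxicity. The bullet would indeed no longer reach their non-indicated use. But the harm there is lost exposure, and stopping sirolimus completes the loss rather than correcting it.

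Fifth, investigators keep wide discretion elsewhere, through the risk-benefit judgement in section 7 and the scheduled evaluations in 1.3.10. That is true. It means that deletion costs nothing in safety, and it gives no reason to keep a ground unrelated to the child's benefit.

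Finally, the size is hypothetical: the number of such stops may be zero, and a child stopped partway may keep some benefit. Both points stand, and they hold the rating at minor.

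**Conclusion.** The point holds as a minor design flaw. Section 7.2 contains a non-safety ground for permanent withdrawal that fits poorly with 5.6.1 to 5.6.3 and has no function in the primary, per-protocol or safety analysis. It can only reduce exposure in the sirolimus arm.

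One affected child of 30 would cost 0.25 to 0.5 points of expected difference and roughly 1 to 4 points of power, depending on the SD and on how much of the effect is lost. These figures rest on the planned effect of 15, normal scores, 10% missing values replaced at random from controls, and an assumed single stop. The protocol gives no basis for a rate. Reasons for stopping must be documented, follow-up may continue, and the child is analysed as randomized, so no bias or false positive arises.

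**What to change.** In the 7.2 bullet, delete the five words that stand between the word toxicity and the word while in "or other substances that, in the opinion of the investigator, are likely to increase toxicity or otherwise confound the results while taking the IMP". Leave the toxicity ground as it is, with no exemption for the drugs in 5.6.1. That ground is needed because section 5.6.1 warns: "Co-administration of sirolimus with strong inhibitors of CYP3A4 or inducers of CYP3A4 is not recommended". It also reports an average 11-fold rise in sirolimus AUC with voriconazole.

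The change can go into the next amendment. It needs no extra data, visits or patients, and it weakens no safety stop.
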